## Abstract

**Background:**

The aging population has led to an increased number of people in nursing homes (NHs). The use of antimicrobials in this setting carries an increased risk of adverse events and interactions, particularly in individuals with advanced age, comorbidities, and polypharmacy. Antimicrobial Stewardship Programs (ASPs) have been shown to reduce the consumption of these drugs, improve prescribing practices, and have a positive ecological impact. However, the implementation of ASPs in NHs remains limited.

**Objective:**

To develop and evaluate the impact of EduFAST web platform, which is designed to train professionals, monitor activities and provide ASP teams with periodic feedback and indicators of antimicrobial use and microbial resistance in NHs.

**Methods:**

Quasi-experimental, multicenter, before-and-after study. The intervention phase will last 12 months and involves implementing ASP strategies (educational measures, indicator monitoring and periodic feedback) via the EduFAST web platform. Information will be collected on the use of the web platform, user satisfaction, knowledge gained and the number of website visits. To assess the impact of EduFAST’s implementation, the following data will be recorded: clinical variables; antimicrobial consumption and prescription profiles; and the incidence of infections caused by multidrug-resistant bacteria and *Clostridioides difficile*. Additionally, the presence and concentration of antimicrobials, multidrug-resistant microorganisms and resistance genes in wastewater from the participating centers will be recorded to evaluate the correlation between clinical samples, antimicrobial consumption and wastewater findings, as well as the environmental impact of the intervention. The intervention’s impact will be analyzed through interrupted time series analysis, trend analysis, mixed linear regression models and correlation analysis for data obtained from wastewater samples.

**Conclusion:**

The aim of this project is to facilitate the implementation and sustainability of ASPs through the development of a national-level website. Wastewater analysis will provide insight into the correlation between antimicrobial consumption, microbial resistance, and the environment from a one-health perspective.

## Introduction

1

Due to the aging of the population, the number of people living in nursing homes (NHs) is increasing. NHs are facilities built specifically for the residential and/or nursing care of older adults with advanced physical and/or cognitive disabilities. Residents very often require personal care and support from healthcare professionals, which makes them vulnerable to easily spreadable infections (1).

In the older population, infectious diseases are one of the most important causes of mortality and have a significant impact on the increasing demand for healthcare and hospital admissions. Urinary, respiratory tract, skin and soft tissue infections are the most common infections in this setting (2, 3). Consequently, antimicrobials are among the most frequently prescribed drugs in NHs. Previous studies point out that 70% of residents receive antimicrobials, and as many as 75% of those antimicrobials were prescribed inappropriately, without adequate documentation or evidence of infection (4).

Antimicrobial Stewardship Programs (ASPs) are the strategy recommended by international organizations to improve the use of antimicrobial agents and combat bacterial resistance (5, 6).

The positive impact of ASPs in hospitals is well-established. ASPs reduce antimicrobial use and improve patient outcomes by reducing infections or colonization with multidrug-resistant (MDR) organisms, as well as reducing costs. However, evidence is still scarce in other settings, such as NHs (7–12). NHs are complex compared with hospital settings, with many factors such as the lack of on-site diagnostic resources, the availability of physicians to evaluate residents before prescribing medications or the quality of the information provided by other healthcare personnel, among others, influencing the prescribing decision-making process and, therefore, the success of ASPs (8). Among the main barriers to the implementation and maintenance of ASPs in this setting are the dispersion and heterogeneity among facilities, as well as the lack of tools for training and the periodic evaluation of process and outcome indicators (13).

On the other hand, the overuse of antimicrobials also results in pharmaceutical contamination. This refers to concerns about the impact of the release of drugs or their metabolites into the environment through urine, feces, and wastewater from urban, hospital, industrial, agricultural or livestock origin (14). Drugs can be excreted in 30–90% unchanged through urine and feces, reaching the environment after wastewater treatment, where removal is often incomplete (15). Consequently, recent studies have observed a correlation between antimicrobial consumption and resistance in wastewater (16).

The relationship between antibiotic use and antimicrobial concentrations in wastewater is garnering interest (17). Exposing bacteria to subinhibitory concentrations of antimicrobials creates the perfect environment for the development of MDR organisms and the transfer of resistance genes (18, 19). Studies conducted in hospital effluents in Japan were able to detect extended-spectrum beta-lactamase (ESBL)-producing enterobacteria, carbapenemase-producing enterobacteria, methicillin-resistant *Staphylococcus aureus* (MRSA), and multidrug-resistant *Pseudomonas aeruginosa* and *Acinetobacter baumannii* at different concentrations (20). A recently published systematic review highlighted that the prevalence of BLEE-producing enterobacteria was 24.8%, mainly *Escherichia coli* BLEE, and that the prevalence was higher in hospital effluents (21). Recent studies have highlighted the correlation between the presence of resistant microorganisms in wastewater and clinical samples (22). For example, carbapenemase genes, such as blaNDM-1 and blaOXA-23, have been identified in treated effluents and are frequently genetically connected to clinical isolates, suggesting a hazardous link between the environment and human infections (23). This has direct implications not only for ecosystems but also for wildlife and human health, as MDR organisms propagate in the environment and may eventually return to humans through the food chain or other pathways (24). On the other hand, these findings also suggest the potential use of wastewater as a non-invasive method for monitoring and surveilling microbial resistance and antimicrobial consumption in healthcare institutions and communities (25, 26).

In light of this situation, the EduFAST project intends to:Design and develop a web platform to train professionals, monitor activities and provide ASP teams with regular feedback and data on antimicrobial use and microbial resistance in NHs.Evaluate the impact of the web platform as an ASP tool.Analyze the relationship between antimicrobial concentrations in wastewater and antimicrobial consumption at the center.Analyze the relationship between the presence of MDR microorganisms and their resistance profiles in wastewater and in clinical and carrier screening samples.

## Materials and methods

2

### Study design and period

2.1

This is a quasi-experimental before-and-after interrupted time series study evaluating the implementation of antimicrobial stewardship strategies through a web platform (EduFAST) for healthcare workers in NHs. The project comprises four phases (Figure 1). The preparation and pre-intervention phase were carried out between January 2024 and June 2025. The study is currently in the intervention phase, which began in July 2025 and will continue until 2026. The results are expected in early 2027.

**Figure 1 fig1:**
[figure not shown]
Phases and timeline of EduFAST project.

### Intervention

2.2

The intervention consists of the implementation of antimicrobial stewardship strategies through the EduFAST web platform in participating NHs, to optimize antimicrobial use, improve infection management, and strengthen surveillance of antimicrobial resistance.

The intervention phase began at the end of 2025 and will continue throughout 2026. During this period, healthcare professionals from participating NHs will have access to the EduFAST platform and will be encouraged to use its different modules as part of routine clinical practice.

The intervention includes three main components:Educational component. Healthcare professionals will have access to training materials hosted on the platform, including treatment guidelines for the most common infectious syndromes in NHs, audiovisual materials, infographics, and simulated clinical cases. Participants will complete questionnaires assessing baseline knowledge, acquired knowledge, and satisfaction with the training activities.Monitoring of antimicrobial use and resistance indicators. Participating centers will enter monthly data on antimicrobial consumption, clinical outcomes, and microbiological indicators. The platform will automatically calculate predefined indicators, allowing centers to monitor antimicrobial use and resistance trends.Results reporting and feedback. The platform will generate periodic reports summarizing the indicators for each participating center. These reports will allow users to compare their center’s results with aggregated data from other participating NHs and will provide recommendations to improve antimicrobial prescribing practices and infection management.

### Selection and inclusion of NHs

2.3

Study information has been distributed via email at a regional level to investigators from public Andalusian NHs who had participated in a different study carried out a few years ago (13), and at a national level through the ASP coordinators of Spain’s autonomous communities. All organizations interested in participating have received an online questionnaire to collect general characteristics of the participating NHs and, at an aggregated level, of their residents (Table 1).

**Table 1 tab1:** The selection questionnaire.

Description	Questions
General information	First and last name
	Contact email address
	Job position: doctor, pharmacist, microbiologist, nurse, nursing assistant, center director, other
	Name of nursing home
	Autonomous community
	Province
	City
Characteristics of nursing homes	Management: public, private, or mixed management
	The center serves users on a continuous basis (institutionalized), on a day basis, or both
	Number of places at the center
	Mean number of residents at the center
	The center cares for: elderly people in situations of dependency; people with physical disabilities; people with mental disabilities; people with mental health problems; people with drug addiction problems; people with chronic and/or disabling somatic illnesses; people convalescing after hospital discharge without sufficient autonomy for self-care; people with terminal illnesses; other
	Mean number of dependent residents at the center
About the center’s team of professionals	Doctor team: the center has its own medical staff available 24 h a day, every day of the week; the center has its own medical staff available less than 24 h a day, every day of the week; the center has its own medical staff available 24 h a day on working days; the center has its own medical staff available less than 24 h a day on working days; the reference medical staff belong to primary care centers; the reference medical staff belong to hospitals; other
	Nursing/Nursing assistant: the center has its own nursing/nursing assistant staff available 24 h a day; the center has its own nursing/nursing assistant staff available less than 24 h a day; other
About the prescription and dispensing of antimicrobials	When necessary, the prescription of antimicrobials is carried out through: private prescription (paper format); public prescription (paper format); electronic prescribing system (private company); electronic prescribing system (within the National Health System); no prescriptions are made at the center; other
	When an antimicrobial is prescribed, the medication is obtained from: community pharmacy; pharmacy service of the hospital of reference for the center; pharmacy service of the nursing home itself; other
	Regarding available data on antimicrobial use, we could know: total defined daily dose (DDD) of antimicrobials; DDD of specific antimicrobials; total number of antimicrobial prescriptions; number of prescriptions for specific antimicrobials; none of the above
	These data can be obtained with the following frequency: monthly; quarterly; biannual; annual; none of the above
About clinical samples for microbiological analysis	When necessary, the microbiological analysis of clinical samples is carried out at: microbiology laboratories of private hospitals; microbiology laboratories of public hospitals; other private laboratories; no samples are taken at the center for microbiological analysis; other
	Data on microbiological isolates from the residents can be obtained with following frequency: monthly; quarterly; biannual; annual; none of the above

#### Inclusion and exclusion criteria

2.3.1

Participation in the study was possible when the NH met the following criteria:Public, private, or mixed management.Minimum center size: 50 continuous institutionalized places.Ability to regularly provide the required clinical data, antimicrobial consumption, and microbial resistance for the project.Commitment and interest in the project and achieving its objectives within the estimated timeframe.

Participation in the study was not be possible when the NH met the following criteria:Centers participating in another project involving the implementation of a strategy for optimizing antimicrobial use and resistance control.

#### Sample size

2.3.2

The sample size has been calculated based on the results of the multicenter study ‘PROA-SENIOR’ (13). Considering an intraclass correlation coefficient of 0.21, a coefficient of variation between center for total antimicrobial consumption (the main variable) of 0.41, and an average of 110 residents per center, with an alpha risk of 5%, a power of 80%, and a detection of the effect size of 20%, the required sample size is 9 centers. Adding a 10% loss, the minimum sample size obtained is 10 NHs. For the wastewater analysis, three participating NHs will be selected.

### EduFAST web platform: design and development

2.4

In terms of technological structure, the web platform will include a backend component, which will provide administration and data management features, and a web platform.

The web platform will consist of the following modules:*General project information module*. It will consist of two sections. The first will contain information about the research project, the web platform, and the research team. The second section will provide information about the participating NHs, with a map showing the location of each center. Access to this module will be public and available to all users.*Training module*. It will include treatment guidelines for the main infectious syndromes in NHs, audiovisual materials, infographics, and simulated clinical cases aimed at healthcare professionals from the participating centers. There will also be questionnaires on prior knowledge, questionnaires to assess acquired knowledge, and a satisfaction questionnaire. Access to this module will be restricted to participants, editors and administrators.*Data entry module*. Participants will be able to enter the numerators and denominators for each study indicator (antimicrobial use indicators, clinical indicators, and microbial resistance indicators). The web platform will then automatically calculate the final value of each indicator. Table 2 shows the indicators with their respective numerators and denominators. Access to this module will be restricted to participants, editors and administrators.*Results presentation and reporting module*. This module will consist of three sections. The first section, “Result Presentation,” will display the indicator results through tables and figures. This section will offer two levels of access: open access for web users, who will be able to view aggregated information on antimicrobial consumption across all participating NHs; and participant access, which will allow users to analyze their own data and compare their center’s results with the aggregated results of other centers with similar characteristics. The second section, “Result Reports,” will allow participants to download personalized reports containing their results, along with key recommendations or strategies to be implemented in the center based on deviations identified in relation to the average value of each indicator. Access to these modules will be restricted to participants, editors and administrators. The third section, “Result Maps,” will display the results of all indicators aggregated by autonomous communities on a map, and will be available only for editors and administrators.*Contact, help, and frequently asked questions (FAQs) module*. It will provide users with information on how to use the tool through materials that include both text and video instructions.*Private area*. This section will provide access to advanced features depending on the user’s role. Participants will be able to view registered users associated with their center, as well as review, modify, or delete related data. Editors/administrators will have access to features related to the maintenance, management, and generation of usage statistics for the web platform (logins, centers, users, generated reports, downloads, and interaction with materials).

**Table 2 tab2:** Indicators from the EduFAST study.

Indicator		Definition
Antimicrobial use indicators	Numerators	Monthly total Defined Daily Dose (DDD) of antimicrobials (ATC groups J01 + J02) Monthly DDD of specific antimicrobials (amoxicillin, amoxicillin/clavulanic acid, cefixime, other cephalosporins, azithromycin, clarithromycin, ciprofloxacin, levofloxacin, moxifloxacin, clindamycin, metronidazole, sulfamethoxazole/trimethoprim, fosfomycin trometamol, and other antimicrobials) Monthly number of total antimicrobial prescriptions (ATC groups J01 + J02) Monthly number of prescriptions of specific antimicrobials
	Denominator	Number of residents in the month
Clinical indicators	Numerators	Monthly number of hospital admissions Monthly number of hospital admissions due to infections Monthly number of hospital admissions due to adverse effects of antimicrobials
	Denominator	Number of residents in the month
Microbiological indicators	Numerators	Monthly number of extended-spectrum beta-lactamase-producing *Escherichia coli* isolates Monthly number of extended-spectrum beta-lactamase-producing *Klebsiella pneumoniae* isolates Monthly number of carbapenemase-producing *Enterobacteriaceae* isolates Monthly number of methicillin-resistant *Staphylococcus aureus* isolates Monthly number of multidrug-resistant *Pseudomonas aeruginosa* isolates Monthly number of multidrug-resistant *Acinetobacter baumannii* isolates Monthly detection of DNA or toxin for *Clostridioides difficile*
	Denominator	Number of residents in the month

The flowchart corresponding to the web platform menu, which can only be accessed by participating users is shown in Figure 2.

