### Statistical analysis

2.9

A descriptive analysis will be performed. Continuous variables will be expressed as measures of central tendency and dispersion, such as mean ± standard deviation or median and interquartile range, depending on the distribution. Categorical variables will be expressed as absolute and relative frequencies.

Interrupted Time Series Analysis (ITSA) will quantify changes in the level (immediate effect) and trend (sustained effect) of outcomes associated with implementing the web platform, considering the study’s longitudinal and ecological nature. ITSA will be performed using a segmented regression model to estimate four parameters: baseline level, baseline trend, the change in level immediately following the intervention, and the change in trend following the intervention. Seasonal adjustment will be applied to those time series in which seasonality were detected. The model incorporates an autoregressive term to account for the autocorrelation present in the time series data. To assess variability and the overall effect across different centers, we will use a linear mixed model (LMM) for repeated measures that includes a random intercept for center. Potential confounders will be managed as fixed effects covariates. *Post hoc* comparisons of estimated marginal means will be performed with the Bonferroni correction applied to adjust for multiple comparisons.

We will evaluate the correlations between the presence of MDR microorganisms and their resistance profiles in wastewater, clinical, and carrier screening samples. We will also evaluate the correlations between antimicrobial concentrations in wastewater and consumption data from centers. We will assess the strength and direction of these correlations using the appropriate Pearson or Spearman correlation coefficient. Then, we will perform univariate and multivariable linear regression analyses to further explore the relationships.

All statistical analyses will be performed using two-tailed tests in IBM SPSS Statistics and R statistical software. A *p*-value of less than 0.05 will be considered statistically significant.

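### The monthly resident denominator is undefined while the data-entry route changes between phases, and the linear mixed model ignores center size: possible small bias and a modest loss of efficiency

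*Protocol article*

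**What the plan says.** **Denominator.** Table 2 in section 2.4 gives all three indicator groups the same denominator, "Number of residents in the month". It serves total DDD as well as counts such as "Monthly number of hospital admissions due to adverse effects of antimicrobials". Resident-days do not appear in the article. Section 2.4 adds that "The web platform will then automatically calculate the final value of each indicator", from numerators and denominators that participants enter. Section 2.5 (Data collection) says that pre-intervention data go into an Excel form and intervention-phase data into the platform. The selection questionnaire (Table 1) asks for the mean number of residents, but Table 2 does not carry that word over.

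**Models.** Section 2.9 states that "Interrupted Time Series Analysis (ITSA) will quantify changes in the level (immediate effect) and trend (sustained effect) of outcomes". It continues: "ITSA will be performed using a segmented regression model to estimate four parameters", and "The model incorporates an autoregressive term to account for the autocorrelation present in the time series data". No error family or link is given for that model. For the effect across centers, the text is explicit: "we will use a linear mixed model (LMM) for repeated measures that includes a random intercept for center". It mentions no exposure offset, count distribution or weight for center size.

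**Center size.** Section 2.3.1 requires "Minimum center size: 50 continuous institutionalized places" and sets no upper limit. Section 2.3.2 names total antimicrobial consumption as the main variable and assumes an average of 110 residents, a between-center coefficient of variation of 0.41 and a 20% effect. The Discussion (section 3) lists heterogeneity between homes, size included, as a limitation and relies on the linear mixed model to handle center effects.

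**The concern.** Two separate things are at stake.

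First, a rate compared before and after is only as good as the constancy of its denominator. Mean census, point census and ever-present residents differ by the turnover within the month. The form, and possibly the person filling it in, changes at about the time the intervention starts. A shift in counting would therefore look like an intervention effect, and it would reach the main variable as well as the secondary ones.

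Second, a monthly rate from a home of 50 is noisier than one from a home of 250. A random intercept lets homes differ in their mean level; it does not let the residual variance depend on size. Each home's change then carries the same weight, and information from the larger homes is under-used. The remedy named in the Discussion does not cover this part of the size problem.

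**Working it through.** **1. The plan's own figure.** Section 2.3.2 gives 9 centers, 10 after loss, and names no formula. A single-group, two-sided before/after calculation gives (1.960 + 0.842)² × 0.41² / 0.20² = 33.0 residents. The design effect is 1 + (110 − 1) × 0.21 = 23.89, so 33.0 × 23.89 / 110 = 7.16 centers. That rounds to 8, or to 9 with one center added for small samples (8.16). A design effect for unequal sizes with CV 0.41, 1 + (1.1681 × 110 − 1) × 0.21 = 27.77, gives 8.33, hence 9. Then 9 / 0.9 = 10. The figure can be reached, and the present point does not depend on it.

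**2. Denominator definition.** With steady occupancy N and monthly turnover t, an ever-present count is N(1 + t), so the rate is divided by 1 + t. The article gives no turnover; the values below are assumed.

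| Monthly turnover | Switch from mean census to ever-present | Reverse switch |
|---|---|---|
| 2% | −2.0% | +2% |
| 5% | −4.8% | +5% |
| 10% | −9.1% | +10% |

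If ever-present is used throughout and turnover rises from 2% to 5%, the ratio moves by 1.02/1.05 − 1 = −2.9%. With a constant definition and constant turnover the bias is zero.

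**3. Month length.** A 31-day month has 31/28 − 1 = 10.7% more days than February. Between periods this nearly vanishes: January 2024 to June 2025 averages 547/18 = 30.39 days and 2026 averages 365/12 = 30.42, a ratio of 1.001.

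**4. Cost of equal weighting.** In a within-center before/after contrast the random intercept cancels. If residual variance is proportional to 1/n, the variance with equal weights relative to size weights is Σ(1/n) × Σn / J², where J is the number of centers. For ten centers with mean 110 (spreads assumed):

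| Sizes | Variance ratio | Relative efficiency |
|---|---|---|
| all 110 | 1.00 | 1.00 |
| 80–140, even | 1.03 | 0.97 |
| 50–170, even | 1.16 | 0.86 |
| 50–270, skewed | 1.30 | 0.77 |
| seven of 50, plus 150, 250, 350 | 1.69 | 0.59 |

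Any monthly variation that does not shrink with size would reduce these losses.

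**5. Power.** Simulation: 10 centers of 50–270 residents, 12 + 12 months, center effects, level shift only, 3,000 runs. Rates are per 1,000 resident-months and assumed, because the article gives none. The month-to-month variation in DDD is also assumed. The last column is a Poisson model with a log(residents) offset for counts and a quasi-Poisson model for DDD.

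| Outcome | Unweighted linear | Weighted linear | Poisson type |
|---|---|---|---|
| Rate 0.5, ratio 0.5 | 0.15 | 0.19 | 0.10 |
| Rate 2, ratio 0.8 | 0.10 | 0.11 | 0.10 |
| Rate 2, ratio 0.5 | 0.46 | 0.56 | 0.55 |
| Rate 10, ratio 0.8 | 0.32 | 0.38 | 0.39 |
| Rate 10, ratio 0.5 | 0.98 | 0.99 | 1.00 |
| DDD, 20% reduction | 0.97 | 0.99 | 0.99 |
| DDD, 10% reduction | 0.45 | 0.53 | 0.54 |

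Under no effect, the linear models rejected in 4.1% to 5.3% of runs for counts and the Poisson model in 3.0% to 5.0%. For DDD the rates were 5.6% (unweighted), 6.2% (weighted) and 6.5% (quasi-Poisson), so a small part of the DDD gain may reflect slight inflation. A further simulation with sizes 50–170 or 50–250 gave gains of 2 to 8 points for moderately sparse counts, and 6 to 7 points with segmented trend terms included.

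**6. Sparsity.** At an assumed 1 isolate per 1,000 resident-months, a home of 110 expects 0.11 per month and has exp(−0.11) = 90% zero months.

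**The case against.** The article never says that the headcount means ever-present residents. Table 1 asks for a mean number of residents, and section 2.3.1 speaks of continuous institutionalized places, so a mean census is at least as natural a reading. Under it, only month length remains, which is about 0.1% between periods and can be partly absorbed by the planned seasonal adjustment. A new entry form need not mean a new way of counting, and nothing suggests that turnover changes. All of this stands. What is left is that the definition is not fixed where it must be constant.

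The article is also a condensed account, and an unseen analysis plan may settle error family, link and weighting. That stands for the segmented regression, whose family is not stated, so it cannot be said that every analysis is linear. It does not remove the point about the mixed model, which is named as linear with a random center intercept and is offered as the answer to heterogeneity.

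Finally, center sizes and event rates are assumed here, and the main simulation leaves out trend and autocorrelation, so the absolute powers are illustrative. Linearity is not the main culprit: size weighting alone recovers nearly all the loss, and at 0.5 events per 1,000 the Poisson model has less power than either linear model. This stands too and shapes the fix.

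**Conclusion.** The point holds in a limited form. The denominator is undefined across a change of data-entry route. A change of definition would shift the rate ratio by about 2% to 9% at an assumed turnover of 2% to 10%; a constant definition with constant turnover leaves no bias. The linear mixed model does not account for variance that depends on center size. Under assumed sizes of 50–170 to 50–270, equal weighting has relative efficiency of about 0.86 to 0.77, and close to 1.0 if the homes are of similar size. For the 50–270 spread this costs roughly 2 to 9 power points for moderately sparse counts where there is power to gain, and 2 to 3 points for total DDD at the 20% effect.

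A reader might infer more, and the article does not support it:
- That the denominator misstates time at risk. This follows only under the ever-present reading.
- That month length distorts the effect by 10.7%. That is the gap between single months, not between periods.
- That the linear analysis is invalid. Its type I error stayed near 5%.
- That the main variable is at serious risk. DDD is not a sparse count, and the loss at the planned effect is small.

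**What to change.** - Define the denominator once, identically in the Excel form and the platform, as mean daily census or, where census records allow, resident-days. Check the baseline data against that definition.
- Analyse prescriptions, admissions and isolates with a Poisson or negative binomial mixed model, with a log-exposure offset and the same segmented terms.
- Weight DDD rates by center size or model them on the log scale. The log scale also gives the effect as a relative change, which is how the 20% target reads beside a coefficient of variation.
- Set a minimum event count below which an indicator is only described, because a count model gains nothing for very rare events.

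The cost is one redefined field, some re-derivation of baseline denominators from center records, and slightly more analysis code. Section 2.5 describes retrospective collection from center records but does not say that daily census records exist. Where they do not, mean census is the workable choice.
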